### Statistical Analysis and Sample Size Calculation

The baseline values of MRI scale scores and cognitive tests (listed in Table 1) will be subtracted from the corresponding follow-up values, and percent change from baseline will be calculated. Based on the PLMI (≥15/h or <15/h), two groups will be formed. In order to reproduce results of the cross-sectional study conducted by Kang et al. (51), group comparisons will be made using the Mann–Whitney test for non-parametric statistics or unpaired *t*-test, depending on whether the distribution is normal. To assess the association between the PLMI and total cerebral SVD sum score, as well as WMH volume, Fazekas Scale score, and Scheltens Scale separately, Spearman correlation analysis will be applied. To confirm the data obtained by Leng et al. (54) and complement it with a more detailed cognitive assessment, logistic regression will be utilized to study the association between PLMS and clinically significant changes in cognition from the baseline to the follow-up visit.

Multiple regression analysis will be used to estimate the capability of each of the characteristics of PLMS (LMs, LMI, PLMI, PI, and SILMS index) to predict each of the outcome variables (except for stroke incidence and mortality rate). Adjustment for main predictors of cardiovascular risk (age, hypertension level, body mass index, diabetes mellitus, ischemic heart disease, cholesterol level, and smoking) will be made to determine if the associations are independent of these factors. Comparison of stroke incidence (separately for cerebral infarct, non-traumatic intracranial hemorrhage, and transient ischemic attack) as well as mortality rate due to stroke between two groups will be made using Pearson's chi-square test.

Spearman correlation test will be applied to evaluate the association between the PLMI and scores of self-reported questionnaires (listed in Table 1) and assess the influence of PLMS on sleep quality, mood, and daytime functioning. The level of statistical significance will be set at *p* < 0.05. All statistical analyses will be performed using SPSS version 21.0 (SPSS Inc., Chicago, IL, USA).

Since the progression of cSVD features depending on PLMI is the key point of our study and linear regression will be applied, we calculated the sample size (N) based on this type of design. As mentioned above, there are seven independent variables (*p* = 7): age, arterial hypertension level, body mass index, blood sugar level, ischemic heart disease, cholesterol level, and smoking duration, and one tested parameter (PLMI or other parameters of PLMS). The sample size should be calculated depending on effect size: N = 392 + p for small, N = 52 + p for medium, and N = 22 + p for large effect size respectively (104). Thus, for revealing medium effect size, N = 52 + 7 = 59 participants should be enrolled, and for revealing small effect size, N = 392 + p, or 392 + 7 = 399 participants should be enrolled. A large effect size of PLMS is not expected. Therefore, 59 patients should be enrolled initially, and when no effect is revealed, the sample size should be enlarged up to 399. On the other hand, a comparison of cSVD feature prevalence between two groups is also planned as interim analysis. For this purpose, unpaired *t*-test (or Mann–Whitney test, depending on whether the distribution is normal) will be applied, and it requires standard deviation (SD) to calculate the sample size. When SD = 1.22 [obtained by Kang et al. (51)] and given probability for rejecting the null hypothesis α = 0.05, probability of failing to reject the null hypothesis under the alternative hypothesis β = 0.2 and effect size = 0.5, group size *N* = 49 is received when rounded up to the next highest integer. Therefore, at least 49^*^2 = 98 patients should be enrolled, but this number could be changed after another value of SD will be received.

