### Hypothesis

PLMI equal to or more than 15 movements per 1 h of sleep is a predictor of small vessel disease progression.

Null hypothesis: the presence of PLMS with index ≥ 15/h has no influence on cSVD course.

Alternative hypothesis (one sided): the presence of PLMS with index ≥ 15/h worsens cSVD course.

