### Outcomes

The primary outcome variable is total WMH volume change in percentage from baseline. The minimal clinically important change would be calculated based on baseline standard deviation as it was suggested by Lemieux et al. (103): the smallest effect size will be calculated by multiplying the baseline standard deviation by 0.2.

The secondary outcomes are the WMH volume change in each area of interests (periventricular, juxtacortical, infratentorial, and deep white matter), change in cognitive performance (results of each test will be processed separately) in percentage from baseline, cerebral infarct incidence, non-traumatic intracranial hemorrhage incidence, transient ischemic attack incidence, and rate of mortality due to stroke.

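### The hypothesis concerns PLMI ≥15/h, but the regression that sizes the study tests five PLMS metrics at unadjusted 0.05 and fixes none of them as the confirmatory exposure

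*Protocol article*

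**What the plan says.** All references are to the protocol article.

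- **Hypothesis.** The claim under test is "PLMI equal to or more than 15 movements per 1 h of sleep is a predictor of small vessel disease progression". The alternative is directional: "Alternative hypothesis (one sided): the presence of PLMS with index ≥ 15/h worsens cSVD course".
- **Outcomes.** There is one primary variable: "The primary outcome variable is total WMH volume change in percentage from baseline". Secondary outcomes include "WMH volume change in each area of interests (periventricular, juxtacortical, infratentorial, and deep white matter" and "change in cognitive performance (results of each test will be processed separately) in percentage from baseline".
- **Statistical Analysis and Sample Size Calculation, analysis part.** The plan reads: "Multiple regression analysis will be used to estimate the capability of each of the characteristics of PLMS (LMs, LMI, PLMI, PI, and SILMS index". The regression is adjusted for cardiovascular risk factors and covers every outcome except stroke incidence and mortality. The significance level is 0.05, with no adjustment stated. The ≥15/h versus <15/h comparison is planned separately as a t-test or Mann–Whitney test, introduced as a way to reproduce a cited cross-sectional study.
- **Same section, sizing part.** The sample size is derived for linear regression with seven covariates and "one tested parameter (PLMI or other parameters of PLMS". Enrolment starts at 59 and goes up to 399 if no effect is found. Which metric and which outcome decide this is not stated. A two-group comparison by the same simple tests is described there as an interim analysis.
- **Discussion.** Baseline differences between the groups are acknowledged as a source of bias. Multiple regression that includes the baseline level is offered as the remedy.

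**The concern.** The exposure in the hypothesis and the exposure in the main model are not the same object. The hypothesis is about a cut-off. The model that carries the confounder adjustment and sets the sample size runs through five movement metrics in turn, and how PLMI is coded in it is not given.

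Two things are at stake. First, on the single primary outcome there are five adjusted tests at 0.05 and nothing that says which one bears on the hypothesis, so the error rate attached to a positive finding is not 5%. Second, the decision to recruit 399 − 59 = 340 further patients rests on a result that could be read from any of the five coefficients. If one is significant at 59 patients and four are not, the text does not settle whether an effect has been found.

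**Working it through.** **1. The plan's own sample sizes.** The stated rules give 52 + 7 = 59 (medium effect) and 392 + 7 = 399 (small effect).

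To see what these sizes buy, I took the F test of one regression coefficient, two-sided alpha 0.05 and power 0.80. I assumed f² = 0.15 for medium and 0.02 for small, because the document gives no f².

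| Variant | Medium | Small |
|---|---|---|
| Noncentrality f²·N, 7 or 8 predictors | 55 | 395 |
| Noncentrality f²·(u+v+1), 7 predictors | 61 | 401 |
| Noncentrality f²·(u+v+1), 8 predictors | 62 | 402 |
| One-sided alpha 0.05 | 43 | 311 |
| **Stated** | **59** | **399** |

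Here u = 1 is the numerator and v the residual degrees of freedom. The stated numbers lie between the two-sided variants. They are therefore sized for one two-sided test of one coefficient, although the alternative hypothesis is one-sided.

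**2. Five metrics on the primary outcome.** With m = 5 tests at 0.05:

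- Independent: 1 − (1 − 0.05)^5 = 1 − 0.774 = 0.226.
- Equally correlated normal test statistics, two-sided, by simulation:

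| Assumed pairwise correlation | P(at least one false positive) |
|---|---|
| 0 | 22.6% |
| 0.3 | 20.9% |
| 0.5 | 18.2% |
| 0.7 | 14.9% |
| 0.9 | 10.2% |

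The document gives no correlations. High values are plausible for some pairs, because LMI is LMs divided by total sleep time and PLMI is built from the same movements.

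**3. Link to the enlargement rule.** Suppose the first 59 patients are part of the 399 and each look uses unadjusted 0.05. The final statistic is then √w·Z₁ + √(1−w)·Z₂ with w = 59/399 = 0.148. The simulated chance of a false positive at either look is:

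- one fixed metric: about 9%;
- any of five metrics: 39% at correlation 0, 32% at 0.5, 26% at 0.7 and 18% at 0.9.

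The 9% belongs to the two looks and would remain with a single metric. The rest comes from leaving the metric open.

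**4. If all five metrics were kept as confirmatory.** Bonferroni gives 0.05/5 = 0.01 per test, and 1 − 0.99^5 = 0.049 overall. Under the f² values above (noncentrality f²·N, 8 predictors), the required N rises to about 82 and 588. Power at 59 and 399 falls to about 0.62 and 0.59. The stated sizes fit one exposure, not five.

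**5. If one metric is named.** A single final test has alpha 0.05 and the stated sizes keep their basis. With noncentrality f²·N, power is 0.83 at 59 and 0.81 at 399 (0.831 and 0.805), whether the model has 7, 8 or 9 predictors. Including baseline WMH therefore does not disturb the sizing.

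**The case against.** The strongest reply is that the protocol already points to a lead exposure and a lead outcome. It names one primary variable, describes progression depending on PLMI as its central question, and forms its groups on the ≥15/h cut-off. Detailed multiplicity rules are commonly left to an analysis plan, which is not shown. Most of this is fair, and it rules out several stronger readings that a reader might infer:

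- **That the regression tries five metrics other than PLMI.** It does not. PLMI is one of the five and four are other metrics.
- **That any one significant metric would confirm the hypothesis.** The document states no such success rule. The error rates above show what an open choice permits, not what the authors say they will do.
- **That the hypothesis never gets an adjusted test.** This is too strong. The Discussion offers regression with the baseline level as the answer to group differences, and the coding of PLMI in the model is simply not stated. What can be said is that no adjusted ≥15/h term is listed.
- **That the whole grid counts.** Five metrics by 15 outcomes (1 + 4 regions + 10 cognitive measures in Table 1) gives 75 tests and 75 × 0.05 = 3.75 expected false positives. Fourteen of the 15 outcomes are secondary, and their handling may lie in the analysis plan. The figure is an illustration at most.

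What the reply does not answer is the sizing text. Having called PLMI central, it opens the tested parameter to other PLMS measures, and it makes enlargement depend on a result it does not define. That is written in the protocol itself, and the choice should be fixed before the results on the first 59 patients are seen.

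**Conclusion.** The point holds in this limited form: for the one primary outcome, the adjusted regression on which the study is sized has no fixed exposure. The hypothesised ≥15/h contrast is not among the terms listed for it, and the enlargement rule inherits the ambiguity. The chance of at least one false positive on the primary outcome is roughly 10% to 23% at a single look, against a nominal 5%. This range rests on assumed equal correlations of 0.9 down to 0 and on two-sided tests at 0.05. The two-look figures in the working also assume cumulative data and no adjustment between looks. This should be corrected, but it does not invalidate the design.

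**What to change.** Before any data are seen, name one confirmatory test: the PLMI term in the adjusted linear model for total WMH progression, with baseline WMH included as the Discussion already intends. Either code PLMI as ≥15/h, which matches the hypothesis as written, or keep it continuous and reword the hypothesis to match. State whether the test is one- or two-sided.

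Define the finding of no effect that triggers enlargement by that test alone. Report LMs, LMI, PI, SILMS index, the other coding of PLMI, the unadjusted group comparison and the Spearman correlations as exploratory, with estimates and confidence intervals. Naming one metric does not remove the error from the two looks (about 9% in step 3 of the working); that is a separate matter.

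The cost is a few sentences, and fewer results can be called significant. The ≥15/h coding also loses information compared with continuous PLMI. As an illustration, assume a normally distributed exposure, a linear effect and 34% of patients above the cut (the prevalence the Introduction gives for people over 60). The share retained is then φ(0.412)²/(0.34 × 0.66) = 0.134/0.224 ≈ 0.60, so about 40% is lost. Continuous PLMI can be shown as a sensitivity analysis.

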## Abstract

**Background:** Cerebrovascular diseases are the leading cause of cognitive decline and dementia. Therefore, the investigation of the potential ways to slow down the disease progression is an important research field. Periodic limb movements in sleep (PLMS) are known to be associated with transient changes in heart rate and blood pressure. These changes might influence the course of cerebral small vessel disease (cSVD). Nevertheless, the clinical significance of PLMS, particularly its influence on cardiovascular diseases course, is still controversial and underinvestigated.

**Methods/design:** Patients from 60 to 75 years old diagnosed with cSVD will undergo nocturnal polysomnography. Subjects with apnea/hypopnea index under 5 will be enrolled. Sleep quality and daytime functioning will be assessed at baseline with self-reported questionnaires. Brain MRI and cognitive assessment will be performed at baseline and in the 2-year follow-up. Progression of cSVD markers and cognitive dysfunction will be compared between patients with PLMS index (PLMI) equal to or more than 15 movements per hour of sleep and controls (PLMI <15/h).

**Discussion:** The negative role of PLMS in cSVD progression and related cognitive decline is expected. We suppose that patients with PLMS tend to worsen in cognitive performance more rapidly than age-, gender-, and comorbidity-matched controls. We also expect them to have more rapid white matter hyperintensities and other cSVD marker progression. The limitations of the study protocol are the short follow-up period, the absence of a treatment group, and inability to make a conclusion about causality.

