## Methods and Design

### Protocol Outline

This study was designed as a prospective observational study. It will be conducted in Moscow, Russia (Department of Neurology, I.M. Sechenov First Moscow State Medical University).

In-patients aged 60–75 diagnosed with cSVD according to current diagnostic criteria and neuroimaging standards (51, 54) will be evaluated for MRI markers of cSVD and cognitive function over a period of 2 years. General assessment of risk factors for cardiovascular disease will include identification of hypertension (office measured off medication conventional blood pressure of at least 140/90 mmHg), measuring total cholesterol level, calculation of body mass index, as well as revealing by self-report and exploring the medical history the presence of ischemic heart disease, diabetes, and heart rhythm disturbances. Additionally, the duration of smoking and habitual alcohol consumption will be assessed. For the latter purpose, a validated Russian version of the Alcohol Use Disorders Identification Test (AUDIT) will be applied (58).

The design of the study is schematically depicted in Figure 1. All enrolled patients will undergo overnight PSG at baseline. Based on PLMI, all patients will be divided into the experimental (PLMI ≥15/h) and control groups (PLMI <15/h). The assessment of the night sleep and quality of daytime functioning will be made at baseline only. Assessment of cognitive function and brain MRI will take place at weeks 0 (baseline) and 104 (2-year follow-up). The details on the applied study techniques and evaluation of night sleep, cognitive function, and MRI are given in parts 2.4, 2.5, and 2.6, respectively. The examination protocol is resumed in Table 1.

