Movements with a duration equal to or more than 0.5 s are regarded as leg movements during the sleep (LMs), and those with a duration of <10 s are candidate LMs (68). Two to four unilateral candidate LMs from the two legs overlapping each other within 0.5-s interval are referred to as one bilateral candidate LM if the total duration is <15 s. The PLMS are defined as candidate LMs series of four or more, separated by more than 5 and <90 s and not interrupted by LM > 10 s (68, 69). The total number of LMs during the sleep will be divided by TST to obtain LMI. The PLMI will be calculated as the number of PLMS per hour of sleep (70). Periodic limb movements during wakefulness (PLMW) are movements that meet the criteria of PLMS but occur during bedtime when patient is awake. PLMAI is a number of associations of PLMS series with EEG arousals per hour of sleep (71). The number of PLMW per hour of wakefulness during bedtime is PLMW index. The number of intermovement intervals that will be 10–90 s long and all in sequences of at least three will be divided by the total number of intervals to calculate the PI (70, 72). This index lies within 0 (absence of periodicity) to 1 (complete periodicity). Total number of doublets of LMs with intermovement interval <10 s is divided by TST to gain SILMS index (73). Experimental and control groups will be formed based on PLMI. The experimental group will include patients with PLMI ≥ 15/h, and the control group will include subjects with PLMI <15/h.

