The reported association between high PLMI and transient sympathetic increase does not clarify whether it is a cause-and-effect connection or these events have the same origin. In this regard, more research using controlled trials is needed to demonstrate the positive impact of prolonged treatment of PLMS on cardiovascular health. The absence of a treated group is also one of the limitations of our study. It could establish the utility of pharmacological reduction PLMS.

Another significant limitation of the proposed study design should be discussed. The baseline level of both cognitive function and WMH volume determinates the speed of further progression of the cSVD. Therefore, the difference between groups at baseline will be the reason for the difference in disease progression. In order to deal with this problem, multiple regression analysis is applied and the baseline level will be included in multiple regression equation. Nevertheless, there is a potential bias related to the eligibility criteria. Only a subgroup of patients with AHI under 5 per hour will be included. Taking into account that the large proportion of cSVD patients has at least mild SOAS, the research will encompass only a small part of cSVD patients. However, we have to exclude even mild SOAS. Obstructive sleep apnea syndrome is accompanied by chronic sleep fragmentation as well as chronic hypoxemia that could worsen cognitive performance. Although the impact of mild SOAS on cognitive performance is still controversial (106–108), we cannot be sure that the presence of this condition will not influence the outcome. Taking into account that LMs in general and PLMS, in particular, could be associated with respiratory events, we would not include patients with even mild OSA with the purpose to avoid the presence of confounding factors.

Notwithstanding these limitations, the results of our study could elucidate the role of PLMS in cSVD progression and provide information about its possible influence on assessed outcomes—cognitive decline progression and MRI changes.

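### Controls are called age-, gender- and comorbidity-matched, but groups are split by PLMI alone, sex is in no adjustment set, and the baseline level promised in the Discussion is absent from the covariate list and the count p = 7

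*Protocol article*

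**What the plan says.** All places are in the protocol article.

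- **Abstract, Discussion paragraph.** PLMS patients are expected to decline in cognition "more rapidly than age-, gender-, and comorbidity-matched controls".
- **Protocol Outline.** "Based on PLMI, all patients will be divided into the experimental (PLMI ≥15/h) and control groups (PLMI <15/h". The Nocturnal PSG section repeats the rule: "Experimental and control groups will be formed based on PLMI". The Participants section and the eligibility criteria give no matching variable, ratio or procedure.
- **Statistical Analysis and Sample Size Calculation, model.** "Adjustment for main predictors of cardiovascular risk (age, hypertension level, body mass index, diabetes mellitus, ischemic heart disease, cholesterol level, and smoking". The same section compares the two groups by unpaired t-test or Mann–Whitney test, with no covariates.
- **Statistical Analysis and Sample Size Calculation, sample size.** "As mentioned above, there are seven independent variables", listed as "age, arterial hypertension level, body mass index, blood sugar level, ischemic heart disease, cholesterol level, and smoking duration, and one tested parameter". This gives p = 7, hence N = 59 for a medium and N = 399 for a small effect.
- **Discussion, limitations.** Baseline cognition and baseline WMH volume are said to drive the speed of progression, and the stated remedy is that "multiple regression analysis is applied and the baseline level will be included in multiple regression equation".

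**The concern.** This is a non-randomised comparison, so its conclusion depends on how the exposed and unexposed patients are made comparable. The abstract tells the reader that this is done by matching on age, sex and comorbidity. Nothing in the Methods does so, and dividing all enrolled patients at a PLMI threshold leaves no room for matching.

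Age and the main comorbidities are at least picked up by the regression. Sex is not picked up anywhere. It is also not among the risk factors that the Protocol Outline says will be assessed, nor in Table 1.

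The second problem concerns the covariate that the authors themselves treat as decisive. The Discussion warns that a baseline difference between groups would produce a difference in progression, and it relies on baseline adjustment to deal with that. The section that specifies the model and counts its terms does not include it. An analyst working from the Statistical Analysis section alone would fit a different model from one who had also read the Discussion. The article also does not say which result, the adjusted regression or the unadjusted group comparison, decides the primary outcome.

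**Working it through.** **Step 1. Set the places side by side.**

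| Factor | Abstract | Group formation | Covariate list | Sample-size list | Discussion |
|---|---|---|---|---|---|
| Age | matched | no matching | yes | yes | – |
| Sex | matched | no matching | **no** | **no** | – |
| Comorbidity | matched | no matching | hypertension, diabetes, ischaemic heart disease | hypertension, blood sugar, ischaemic heart disease | – |
| Baseline WMH or cognition | – | – | **no** | **no** | **included** |

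Sex is the one factor claimed as controlled that is handled nowhere. Baseline level is promised in one place and omitted in two. The two lists also differ from each other: diabetes mellitus against blood sugar level, and smoking against smoking duration.

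**Step 2. Reproduce the stated sample size.** The article's rule is N = 52 + p (medium) and N = 392 + p (small). It counts the covariates in p and leaves out the tested PLMS parameter.

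- p = 7: 52 + 7 = 59 and 392 + 7 = 399. Both stated figures reproduce.

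**Step 3. Apply the same rule to the corrected model.**

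- Baseline value only, as the Discussion promises, p = 8: 52 + 8 = 60 and 392 + 8 = 400.
- Baseline value and sex, p = 9: 52 + 9 = 61 and 392 + 9 = 401.
- If the PLMS parameter were also counted, p = 10: 62 and 402.

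**Step 4. Check the cost in power at the stated N.** The article gives no numerical f², so f² = 0.15 (medium) and f² = 0.02 (small) are assumptions. So is a two-sided 5% test, because the Hypothesis section is one-sided and the analysis section does not state sidedness. The test of one coefficient uses a noncentral F with 1 and N − k − 1 degrees of freedom and λ = f² × N, where k is the number of covariates plus one.

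- N = 59, λ = 0.15 × 59 = 8.85. With 7 covariates (k = 8, 50 denominator df) power is 0.831. With 9 covariates (k = 10, 48 df) it is 0.830.
- N = 399, λ = 0.02 × 399 = 7.98. Power is 0.8045 with 7 covariates and 0.8045 with 9.

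The two extra terms cost two patients under the article's rule and at most about 0.001 in power.

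**The case against.** The strongest reply is that baseline adjustment is already planned. The Discussion names the problem and commits to the remedy, and the list in the Statistical Analysis section is introduced as a set of cardiovascular risk predictors, so it need not be the whole model. This largely stands. A reader of the Methods alone might infer that baseline WMH is left out of the analysis altogether; the document does not support that. What remains is a contradiction, because the sample-size paragraph counts the model's terms and arrives at seven without it.

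A second reply is that regression is already the main analysis. The sample size is built on it, and the group tests are introduced as a way to reproduce an earlier cross-sectional study. That is a fair reading, but the article never states that the regression decides the primary outcome.

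A third is that the abstract's sentence voices an expectation and uses the word loosely, for groups made comparable by adjustment. Even so, it names sex, and no adjustment includes sex.

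Some stronger readings are tempting and should be resisted:

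- **That the exposed group will start with worse WMH.** The Introduction cites cross-sectional associations in that direction, but the Discussion says two earlier cross-sectional studies reached opposite conclusions. Imbalance is foreseeable, not established.
- **That the bias can be expressed as a share of the planned effect.** Dividing 0.5 by the SD of 1.22 gives 0.41 SD. However, those inputs belong to the interim group comparison, and 0.41 SD does not lead to the stated 49 per group (it needs 74 one-sided or 94 two-sided).
- **That any bias would favour the hypothesis.** The primary outcome is percent change, so baseline WMH is its denominator. For equal absolute growth, a larger baseline gives a smaller percentage. The sign is open.
- **That the alcohol questionnaire is collected and ignored.** It serves an exclusion criterion and is among the questionnaires to be correlated with PLMI.

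**Conclusion.** The point holds in three parts. The matching claim in the abstract has no counterpart in the design. Sex is controlled neither by design nor by analysis. The baseline level is promised in the Discussion but missing from the covariate list and from p = 7. In addition, the group comparisons are unadjusted and are not ranked against the regression.

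This is a matter of confounding control and internal consistency, not of power. Under the article's own rule the corrected requirement is 61 instead of 59, or 401 instead of 399. The power comparison (0.831 against 0.830 at N = 59) rests on the assumed f² = 0.15 and a two-sided 5% test. No figure is given for the bias in percent WMH change, because neither its size nor its direction follows from the document.

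**What to change.** 1. Delete the matching claim from the abstract.
2. In the Statistical Analysis section, add sex and the baseline value of each outcome to the regression model (baseline WMH volume for the primary outcome, the baseline test score for each cognitive outcome). State that sex is recorded at baseline.
3. In the sample-size paragraph, set p = 9, which gives N = 61 for a medium and N = 401 for a small effect. Use the same definitions of diabetes and smoking in both lists.
4. State that the adjusted regression is the primary analysis of WMH change, and that the t-test or Mann–Whitney comparison is unadjusted and supportive.

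The cost is a change of wording, two degrees of freedom and two more patients. Baseline WMH volume and the baseline cognitive scores are already scheduled in Table 1. Sex is not listed there, but it is routine demographic data.

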#### Non-inclusion Criteria

History of symptomatic stroke, brain tumor, or traumatic brain injury—assessed by clinical history.Hypothyroidism, B12 deficiency, HIV/AIDS, neurosyphilis, autoimmune, and connective tissue diseases—assessed by clinical history.

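### Pearson's chi-square, with no small-count alternative, is fixed for four separately tested stroke outcomes whose expected counts are probably too low for it at 59 or 98 patients

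*Protocol article*

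**What the plan says.** In the protocol article, Statistical Analysis and Sample Size Calculation, the event outcomes are compared "separately for cerebral infarct, non-traumatic intracranial hemorrhage, and transient ischemic attack", and the same sentence adds that "mortality rate due to stroke between two groups will be made using Pearson's chi-square test". That makes four tests. The same section sets one threshold for all analyses ("The level of statistical significance will be set at" p < 0.05) and leaves stroke incidence and mortality out of the regression models. The chi-square test is therefore the only planned inference on these outcomes. For continuous variables the section does give a fallback (t-test or Mann–Whitney, depending on the distribution). For event counts it gives none.

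On size, it says "59 patients should be enrolled initially, and when no effect is revealed, the sample size should be enlarged up to 399". For the two-group comparison it asks for 49 per group, 98 in all, a number it allows to change. Under Non-inclusion Criteria, one entry is "History of symptomatic stroke, brain tumor, or traumatic brain injury". Follow-up is 2 years, which the Discussion calls short. The groups are formed by observed PLMI. The Introduction gives a PLMS prevalence of about 34% above age 60, and says that prevalence in cSVD has not been evaluated.

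**The concern.** Pearson's chi-square relies on a large-sample approximation, and the usual working rule asks for expected counts of at least 5. Stroke subtypes and stroke death, taken one at a time over 2 years in a small cohort without previous symptomatic stroke, may produce only a handful of events. When the PLMS group is the smaller one, the test then reacts to very few events in that group and hardly at all to the same number among controls.

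That is the direction of the study's own hypothesis: "Alternative hypothesis (one sided): the presence of PLMS with index ≥ 15/h worsens cSVD course". The Discussion also says that the protocol allows the influence of PLMS on stroke incidence to be estimated. A claim that PLMS raises stroke risk could thus rest on one to four events and a p-value that an exact test would not support.

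**Working it through.** **Inputs.** From the article: N = 52 + 7 = 59, 49 × 2 = 98 and 392 + 7 = 399 (the sums are correct), with p < 0.05. The plan states no event rate and no power for the chi-square tests, so there is no figure of its own to reproduce for them. Assumed: a 2-year risk of 0.5 to 5% per endpoint; a PLMS share of 34% (20/39, 33/65, 136/263), with 20%, 40% and 1:1 as alternatives; and the uncorrected two-sided test on 1 degree of freedom.

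**Step 1: expected counts.** The smaller expected event cell is E = n₁ × risk. It reaches 5 when the risk is 5/n₁.

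| N | 34% share | 1:1 |
|---|---|---|
| 59 | 5/20 = 25% | 5/29 = 17% |
| 98 | 5/33 = 15% | 5/49 = 10% |
| 399 | 5/136 = 3.7% | 5/199 = 2.5% |

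Even at a 5% risk and 49/49, E = 49 × 0.05 = 2.45. Across the assumed range, every such count at N = 59 or 98 is below 5. At N = 399 and a 34% share, Pearson becomes acceptable from a risk of about 3.7%.

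**Step 2: small tables.** For k events in the PLMS group (n₁) and none in controls (n₂), X² = N·k·n₂ / [n₁(N − k)]. For k = 2 at 33/65, X² = 98 × 2 × 65 / (33 × 96) = 4.02, so p = 0.0449. The Fisher probability is (33 × 32)/(98 × 97) = 0.111. The other rows are obtained in the same way.

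| Split | Events | Pearson p | Fisher p |
|---|---|---|---|
| 20/39 | 2 v 0 | 0.0445 | 0.111 |
| 33/65 | 2 v 0 | 0.0449 | 0.111 |
| 136/263 | 2 v 0 | 0.0487 | 0.116 |
| 12/47 | 1 v 0 | 0.046 | 0.20 |
| 20/78 | 1 v 0 | 0.047 | 0.20 |
| 39/59 | 3 v 0 | 0.031 | 0.060 |
| 49/49 | 2 v 0 | 0.153 | 0.495 |
| 49/49 | 4 v 0 | 0.041 | 0.117 |

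With both events among controls at a 34% share, Pearson gives p = 0.30 to 0.31.

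**Step 3: type I error.** Binomial enumeration with the same true risk in both groups:

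- *34% share, risks 0.5 to 5%.* The two-sided size is 0.4 to 4.2% (N = 59), 0.9 to 4.2% (N = 98) and 4.2 to 5.2% (N = 399). At N = 59 and 98 nearly all of it lies on the harm side, up to about 4.1% against a nominal 2.5%. At 33/65 and a 2% risk, Pearson's size is 3.95%, all toward harm, and Fisher's is 0.9%.
- *20% share, 2% risk.* Tables with at least one PLMS event and no control event are all rejected. At 12/47 they alone contribute (1 − 0.98¹²) × 0.98⁴⁷ = 0.215 × 0.387 = 8.3%. Adding the remaining rejected tables brings the size to about 9% at both 12/47 and 20/78.
- *49/49, 2% risk.* Pearson's size is 1.3%, split evenly between the two directions.

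**The case against.** Three stronger readings are tempting, and the documents support none of them.

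- **Two events against none will be called significant.** This needs both events in the PLMS group and a PLMS share of no more than about 34 to 35%. One patient moved at N = 59 (21/38) gives p = 0.053, and 35/63 gives 0.055. At 49/49, the only split that the plan states, p = 0.153. The 34% is a figure for older people in general. The cohort also excludes restless legs syndrome and sleep apnea, both of which the Introduction links to PLMS, so the figure may not carry over.
- **Counts will be near zero.** No event rate is given. At N = 399, a 3% risk would yield 399 × 0.03 = about 12 events and a smaller expected cell of 136 × 0.03 = 4.1.
- **The test inflates the type I error in general.** At a 34% share, the two-sided size stays at or near 5%. The harm-side excess is also absent in part of the range: at 33/65 and a 1% risk it is 2.25%, below the nominal 2.5%.

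It can also be said that these are secondary outcomes and that a condensed article may leave a small-count rule to the analysis plan. The first part stands and limits the consequence. The second carries less weight, because the article names the test outright and, for continuous data, does name a fallback.

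**Conclusion.** The point holds in a conditional form. Naming Pearson's chi-square alone is a poor choice for these four outcomes at 59 or 98 patients, provided the per-endpoint risk is well below the 10 to 25% that would be needed. That is an assumption, though a reasonable one for patients without prior symptomatic stroke.

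The size of the harm depends on the unknown split. At about one third PLMS, the problem is fragile p-values and a one-directional error of up to about 4.1% against 2.5%. At 20%, a single event suffices and the true error is about 9% at a 2% risk. At 1:1, overall size is close to or below 5%, but four against none is still declared positive where the exact test gives 0.117. At 399 patients the concern fades once the risk is about 3.7% or more (34% share). The primary WMH outcome and the regression analyses are not touched.

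**What to change.** In Statistical Analysis and Sample Size Calculation, replace the chi-square sentence with a rule: Fisher's exact test (or its mid-p version) whenever any expected count is below 5, an exact confidence interval for the risk difference, and a statement that these secondary event comparisons are descriptive. A composite of any stroke or TIA is optional and not needed for the correction.

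The cost is one sentence, with no added patients or data. The drawback is conservatism: Fisher's true size is about 0.9% at 33/65 and a 2% risk. Mid-p lessens this at some splits but not all. It halves the probability of the observed table, so 3 v 0 at 39/59 goes from 0.060 to 0.030, while 2 v 0 at 33/65 goes from 0.111 to 0.056 and stays non-significant. The version should be chosen before any event data are seen.
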